### Sample size

DOORS-D and DOORS-M both aim to recruit 50 patients. Sample size calculations for DOORS-D have determined that for a cohort of 50 patients a 40% prevalence of uterine sarcoma (20 cases) would give a 95% confidence interval of width 0.247 for a sensitivity of 0.95 (95% CI: 0.751–0.999). DOORS-M aims to recruit 50 patients with a previous diagnosis of uterine sarcoma. Given the high rate of uterine sarcoma recurrence, recruitment will be achievable within the study duration, given that the University Hospitals of Leicester currently discusses more than 50 patients with ‘suspicious looking fibroid, sarcoma cannot be excluded’ in the multidisciplinary team meetings per year of which 7–10 are confirmed to be a sarcoma on histology examination.

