Liquid biopsies based on circulating tumour DNA (ctDNA) are rapidly becoming established as a minimally invasive tool for diagnosis, guiding treatment regimens and monitoring for recurrence [25]. The evidence to support a role in the monitoring and detection of endometrial cancer recurrence is increasing [26–29] with a higher diagnostic accuracy compared to the currently available tumour markers, CA125 and HE4 [30]. The potential of the ‘liquid biopsy’ to monitor uterine sarcomas has been explored in previous studies where ctDNA has shown promise as a marker both in the monitoring [31–33] and diagnosis [24] of uterine sarcomas, although other analytes including microRNAs have also been shown to have potential as biomarkers [34]. Leiomyosarcomas were the most common histological subtype investigated and there was significant heterogeneity in terms of both laboratory approaches and the reporting of these approaches. Given the small number of uterine sarcoma cases in the majority of the studies to date, the proportion of cases with detectable ctDNA is currently unknown, and there is no cost-effective test that could give a result in a short time frame to guide patient management, thereby reducing pre-operative diagnostic uncertainty.

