### Study population

DOORS-D will recruit women due to undergo surgery, either hysterectomy or myomectomy, for a suspected uterine sarcoma or a fibroid, whereas DOORS-M will recruit patients who have already received a uterine sarcoma diagnosis within the previous 10 years. Adult females aged 18–99 years, who meet the above criteria, are willing and able to consent to participate in the trial, and understand study requirements, with interpreter support if needed, will be offered recruitment.

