## Discussion

The DOORS-D and DOORS-M studies aim to explore the potential of a ctDNA-based approach to uterine sarcoma management and have the potential to give greater insights into the landscape and challenges of differentiating uterine sarcomas from uterine fibroids. Each study aims to recruit 50 patients, to attain 20 sarcoma cases (40% prevalence) in DOORS-D and 50 cases in DOORS-M. Although this is a large number of cases for a rare malignancy, there is the possibility that our cohort may not include rarer subtypes. The developed ctDNA test through these studies would be trialled in a larger uterine sarcoma population, thereby determining diagnostic ability and enabling test modification. Such an approach has been explored previously [24] however, as yet there is no test that can be used in everyday clinical practice to guide patient management. Also, there is a need for greater understanding of the genomic landscape of sarcomas from women of Black ethnicity to ensure that any test that is developed has equitable diagnostic accuracy, unlike other tests currently used to diagnose endometrial cancer, for example the transvaginal ultrasound scan which has a lower diagnostic ability in women of Black ethnicity [38]. The studies include qualitative interviews to ensure that patients’ voices and opinions are heard and are able to contribute to the future development of blood test diagnosis or monitoring for uterine sarcomas. In addition, exploration of opinions and experiences of women from ethnic minority populations is essential in determining the potential impact for such a ‘test’ due to the significantly poorer long-term uterine cancer survival rates [39] and greater prevalence of uterine fibroids [7]. Previous work that the research team has undertaken, identified a lack of awareness of uterine malignancy amongst women from Black ethnic populations resident in England [40] and although efforts are being undertaken to raise awareness of the signs and symptoms of uterine cancer [41, 42], these focus typically on the symptom profile associated with endometrial cancer rather than uterine sarcomas.

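### The DOORS-D precision rests on 20 sarcomas in 50 patients (40%), which the protocol's own case-flow figures do not support

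*Protocol article*

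**What the plan says.** The Sample size section sets the target: "DOORS-D and DOORS-M both aim to recruit 50 patients". For DOORS-D it then states that "for a cohort of 50 patients a 40% prevalence of uterine sarcoma (20 cases) would give a 95% confidence interval of width 0.247", with the interval given "for a sensitivity of 0.95 (95% CI: 0.751–0.999". The Discussion repeats the 20 cases as an aim: "to attain 20 sarcoma cases (40% prevalence) in DOORS-D".

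The same Sample size paragraph gives the only case-flow data in the article. It says that "the University Hospitals of Leicester currently discusses more than 50 patients with" a suspicious-looking fibroid each year, "of which 7–10 are confirmed to be a sarcoma on histology examination". The Study design section describes DOORS-D as single centre, at that hospital.

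Under Study population, DOORS-D takes women having a hysterectomy or myomectomy "for a suspected uterine sarcoma or a fibroid". The Abstract is a little narrower and speaks of a large fibroid.

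**The concern.** The assumed prevalence is at least twice what the site's own figures suggest. Twenty sarcomas in 50 is 40%, whereas 7–10 in every 50 or more suspicious cases is about 14–20%. No section gives a reason for 40%. Including women with a fibroid would tend to lower the proportion further, since the Introduction puts unexpected sarcoma at fibroid surgery at 0.175 to 0.67%.

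Sensitivity for sarcoma is the only quantity on which DOORS-D is sized, and its precision depends on the number of sarcomas, not on the 50 patients. With half that number or fewer, the estimate is much less precise than a reader of the article would expect. The loss falls mainly on the lower limit, which says how many sarcomas the test might miss.

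**Working it through.** **Inputs.** From Sample size: N = 50; 20 sarcomas (40%); sensitivity 0.95; more than 50 suspicious cases discussed a year, 7–10 of them sarcoma. From Study timelines: opening on 14/07/2025 and recruitment to 29/02/2028. From Ethical approval and trial registration: recruitment to 31/01/2028. Both end dates are used below.

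**1. Reproduce the stated interval.** The exact (Clopper-Pearson) 95% limits for x of n are the 2.5% quantile of Beta(x, n − x + 1) and the 97.5% quantile of Beta(x + 1, n − x). For x = 19, n = 20 they are 0.751 and 0.999, width 0.247. This matches. The Wilson width (0.227) and the Wald width (0.191) do not, so the exact method was used.

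**2. Proportion implied by the site's figures.** 7/50 = 14% and 10/50 = 20%, slightly less if the denominator exceeds 50. These are shares of patients discussed, not of patients operated on.

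**3. Yield if recruitment is unselected.** 50 × 0.14 = 7 and 50 × 0.20 = 10 sarcomas, leaving 43 and 40 non-sarcomas. Exact 95% intervals for sensitivity:

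| Sarcomas | Detected | 95% CI | Width |
|---|---|---|---|
| 7 | 6 | 0.421–0.996 | 0.575 |
| 7 | 7 | 0.590–1 | 0.410 |
| 10 | 9 | 0.555–0.997 | 0.442 |
| 10 | 10 | 0.692–1 | 0.308 |
| 20 (as planned) | 19 | 0.751–0.999 | 0.247 |

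Even with no case missed, 7–10 sarcomas do not reach a width of 0.247.

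**4. What 40% would require of surgical selection.** If every sarcoma discussed goes to surgery and no routine fibroid is enrolled, 40% needs 7/0.40 = 17.5 to 10/0.40 = 25 patients operated on for every 50 discussed, so about 18–25. The documents do not give the actual share.

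**5. What 20 cases would require over the window.** 14/07/2025 to 31/01/2028 is 931 days (2.55 years); to 29/02/2028 it is 960 days (2.63 years).
- Sarcomas in this stream: 7 × 2.55 = 17.8 up to 10 × 2.63 = 26.3, so about 18–26.
- Share needed for 20 cases: at 10 a year, 20/26.3 = 76% (later date) or 20/25.5 = 78% (earlier date). At 7 a year, 20/18.4 = 109% or 20/17.8 = 112%.
- Non-sarcomas must at the same time be held to 50 − 20 = 30.

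**6. Specificity for the matching counts.** With one false positive: 39/40 gives 0.868–0.999 and 42/43 gives 0.877–0.999. The 20-case split leaves 30 non-sarcomas, and 29/30 gives 0.828–0.999.

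**The case against.** Several points on the other side are sound.

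- The arithmetic is right and the statement is conditional: it gives the width that a 40% prevalence would produce. The fault lies in the input.
- The 14–20% describes multidisciplinary team discussions under one label. Women who have surgery are a different denominator. If fewer than about half of those discussed are operated on, prevalence among suspected cases could approach 40%. More overt sarcomas might also reach surgery without that label. The figures also follow the DOORS-M target in the text, although they describe the suspected-sarcoma population at the only DOORS-D site.
- With more than 50 suspicious cases a year and only 50 places, some selection is unavoidable, and the article does not say that recruitment is consecutive. The stream's total of 18–26 sarcomas makes 20 conceivable under strong selection.
- Sampling detail may sit in the full protocol, so a missing quota rule is not in itself a fault of the article.
- DOORS-D is exploratory, and accuracy is reported descriptively.

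A reader might therefore infer too much: that prevalence cannot exceed 14–20%, or that 20 cases will not be reached. The documents support neither. A binomial calculation puts the chance of at least 20 sarcomas in 50 at 0.0009 for a 20% prevalence, but it assumes unselected recruitment, which the article does not state. It cannot carry a claim of failure.

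A reader might also call the sensitivity of 0.95 an error because "the proportion of cases with detectable ctDNA is currently unknown". One illustrative value is not an error, and this is secondary. It does show that the stated width is near the favourable end: 16/20 gives 0.563–0.943, width 0.379.

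None of this supplies a basis for 40%. The only figures given point lower, and the open fibroid eligibility pushes the same way.

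**Conclusion.** The point stands as an unsupported planning assumption. The stated interval is correct for 19 of 20, but the article's own case-flow figures do not lead to 20 sarcomas in 50, and they sit in the same paragraph.

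Under unselected recruitment at the site's rate, about 7–10 sarcomas are expected, with exact widths of 0.31–0.58 for no or one missed case. With one case missed, the lower limit falls from 0.751 to 0.421–0.555.

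This rests on two assumptions: that the share of sarcomas among patients discussed carries over to those enrolled, and that enrolment does not favour sarcomas. If either fails, the yield could be higher. Reaching 20 would still need roughly 76–112% of the sarcomas in this stream, with non-sarcomas held to 30. The proper conclusion is that 20 cases are not shown to be achievable.

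**What to change.** Keep 50 patients and change the text:

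1. In Sample size, replace the single 40%/20-case statement with the precision expected at the site's own case rate: exact intervals for 7 and 10 sarcomas, with 20 shown as best case.
2. Add specificity for the matching non-sarcoma counts, for example 39/40 and 42/43. Use 29/30 only beside the 20-case scenario.
3. Bring the 20-case sentence in the Discussion into line.

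If 20 cases are to stay as the planning figure, justify 40% from the site's surgical data, including the share of discussed patients who have surgery, or state how cases are selected. In the latter case, add that favouring suspicious cases changes the case mix, and with it the population to which sensitivity and specificity apply.

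The cost is a rewritten paragraph and one Discussion sentence, with no extra patients. The downside is that the stated precision becomes less favourable.

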### Study population

DOORS-D will recruit women due to undergo surgery, either hysterectomy or myomectomy, for a suspected uterine sarcoma or a fibroid, whereas DOORS-M will recruit patients who have already received a uterine sarcoma diagnosis within the previous 10 years. Adult females aged 18–99 years, who meet the above criteria, are willing and able to consent to participate in the trial, and understand study requirements, with interpreter support if needed, will be offered recruitment.

### Consent procedures

Potential participants will be given a participant information sheet, the opportunity to ask questions, and be given at least 24 hours decision time before consent is taken. Written consent will be taken by a member of the clinical research team and will include a discussion on the aims and objectives of the study, the study processes and potential risks. It will be explained to the potential participant that they are free to withdraw at any time, they are not obliged to give a reason, and that this will not impact on their future care. Women who do not have English as their primary language will be offered an interpreter to support the consent process.

### Study processes – DOORS-D

The schedule of enrolment, interventions and assessment for DOORS-D are described in Fig 1 [36].

**Fig 1 pone.0339336.g001:**
[figure not shown]
Participant timeline: Schedule of enrolment, interventions, and assessments for DOORS-D.

Participants recruited to DOORS-D study will have a Case Report Form (CRF) completed detailing their demographic characteristics, medical history, and current clinical episode. Pre-operative radiological imaging, including ultrasound scans, CT/MR/PET scans will undergo a blinded review by the study radiologist, and representative images selected for future AI analysis. The analysis plan using radiomics and large language models has not been determined *a priori* due to rapid changes within the field. Prior to surgery 20mls of blood will be collected, processed into plasma and stored for batched ctDNA analysis. The histological diagnosis from surgery will be classified into 1) uterine fibroid; 2) uterine sarcoma; or 3) smooth muscle tumour of uncertain malignant potential (STUMP). A blinded pathological review will be undertaken by the study pathologist to confirm the diagnosis. Participants diagnosed with a sarcoma or STUMP will be offered recruitment to the DOORS-M study. DNA will be extracted from pathology blocks, either fresh or formalin fixed, for whole exome sequencing (WES). Following surgery, a subset of participants will be invited to an interview to discuss their experiences of the study. Recruitment will be purposeful in order to ensure a breadth of opinions from participants from diverse age, socioeconomic and ethnic populations. The interviews will be transcribed verbatim using Microsoft Teams and will be analysed using a reflexive thematic analysis, as described by Braun and Clarke [37].

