## Abstract

Uterine sarcomas can be difficult to differentiate from uterine fibroids due to many shared symptoms and imaging features, which can result in delayed or missed diagnosis, or over treatment. The ‘Development of a blood test for uterine Sarcoma – Diagnosis’ (DOORS-D) (ISRCTN14800787) and ‘Development of a blood test for uterine Sarcoma – Monitoring’ (DOORS-M) (ISRCTN14174468) studies aim to explore the role for circulating tumour DNA (ctDNA) to diagnose and to monitor uterine sarcomas. DOORS-D will recruit patients who have a suspected uterine sarcoma or large fibroid and are due to undergo surgery (hysterectomy or myomectomy) for a blood sample prior to surgery whereas DOORS-M will recruit patients who have been diagnosed with a uterine sarcoma in the previous 10 years for longitudinal blood sampling every 3–6 months over the course of the study. Information will be collated on patient characteristics and symptoms, tumour characteristics and diagnostic imaging, with representative images selected and analysed using large language models. Analysis of genomic/methylation profile of ctDNA samples collected from DOORS-M will be used to design a ctDNA-based ‘test’. Analysis of the samples collected from the participants recruited to the DOORS-D study will enable the accuracy of the ‘test’ to differentiate uterine sarcomas from fibroids to be determined. In addition, the opinions of patients with a suspected or confirmed sarcoma will be explored through semi-structured qualitative interviews. Purposeful recruitment strategy will ensure that the experiences of women from diverse socioeconomic, cultural and ethnic backgrounds are included. The results of the studies will be shared through conference presentations and peer-reviewed publications.

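### DOORS-D sarcoma patients may enter DOORS-M, whose ctDNA data shape the test later assessed in DOORS-D; with no stated separation, DOORS-D sensitivity may be optimistic

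*Protocol article*

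**What the plan says.** The Abstract sets out two stages. First, "Analysis of genomic/methylation profile of ctDNA samples collected from DOORS-M will be used to design a ctDNA-based" test. Then samples from "participants recruited to the DOORS-D study will enable the accuracy of the ‘test’ to differentiate uterine sarcomas from fibroids to be determined".

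Study processes – DOORS-D (text under Fig 1) links the two cohorts: "Participants diagnosed with a sarcoma or STUMP will be offered recruitment to the DOORS-M study". The DOORS-M entry criterion in Study population is that "DOORS-M will recruit patients who have already received a uterine sarcoma diagnosis within the previous 10 years". It does not exclude women who came through DOORS-D.

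Under Sample size, "DOORS-D and DOORS-M both aim to recruit 50 patients", and the DOORS-D precision calculation assumes "for a cohort of 50 patients a 40% prevalence of uterine sarcoma (20 cases"), with a sensitivity of 0.95 and a 95% CI of 0.751–0.999.

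The Analysis section reports sensitivity, specificity and diagnostic accuracy descriptively. It mentions no separation of design and evaluation patients.

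**The concern.** A sensitivity estimate describes performance in new patients only if the cases tested played no part in building the test. Here a woman can give a pre-operative DOORS-D sample, be diagnosed with sarcoma, join DOORS-M, contribute tumour sequence and later plasma to the profiles from which the test is designed, and then be counted as a DOORS-D case when the test is assessed. Markers or thresholds chosen partly because they fit her tumour are more likely to detect her.

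The error runs in one direction, towards a test that looks more sensitive than it is. Sensitivity is the quantity on which the DOORS-D sample size rests, and for a test meant to catch unsuspected sarcoma, overstating it is the more serious kind of mistake.

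**Working it through.** **1. The plan's own figure.** Cases = 50 × 0.40 = 20. The exact (Clopper-Pearson) 95% CI for 19/20 is 0.7513–0.9987, width 0.2475. This reproduces the stated 0.751–0.999 and 0.247. The interval presumes that the 20 cases are independent of test design.

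**2. How large the overlap could be.**
- DOORS-D is single-centre at Leicester (Study design). DOORS-M blood is also taken only at Leicester (Study processes – DOORS-M). The plasma design set and the evaluation set therefore come from one hospital.
- Leicester confirms 7–10 sarcomas a year (Sample size). Recruitment runs from 14/07/2025 to 31/01/2028 (Ethical approval and trial registration) or 29/02/2028 (Study timelines), that is 2.55 or 2.63 years. Incident cases: 7 × 2.55 ≈ 18 to 10 × 2.63 ≈ 26.
- The 20 planned DOORS-D sarcomas would thus be most of Leicester's new cases in the period.
- If all 20 accept, they are 20/50 = 40% of DOORS-M. Participants from other sites give no blood, so if they count towards the 50, the crossover share of the plasma design set is higher than 40%.

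**3. Whether timing separates the sets.** It does not. DOORS-D plasma is stored for batched analysis, genomic results are expected after recruitment ends, and the ctDNA technique is not fixed in advance. Crossovers' data can be in hand when the test is designed.

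**4. Ceiling on the bias.** Let s be sensitivity in unseen patients and f the share of DOORS-D sarcomas also used in design. Assume that every overlapping case is called positive:

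apparent sensitivity = f × 1 + (1 − f) × s

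| s (assumed) | f = 25% | f = 50% | f = 100% |
|---|---|---|---|
| 0.70 | 0.775 | 0.85 | 1.00 |
| 0.80 | 0.85 | 0.90 | 1.00 |
| 0.90 | 0.925 | 0.95 | 1.00 |

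For example, 0.5 + 0.5 × 0.70 = 0.85. Neither s nor f is given in the article.

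**5. Illustration without the ceiling assumption.** All settings here are assumed. There are 2000 uninformative markers, each present in 5% of cases; the 10 most frequent in 50 design cases form the test; a case is positive if it carries any of the 10. True sensitivity is 1 − 0.95^10 = 0.40. Mean apparent sensitivity in 20 evaluation cases was 0.39 with none shared, 0.60 with 10 shared and 0.82 with all 20 shared. This shows the mechanism and its direction. It does not forecast this study.

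**6. Precision under two remedies.** Leaving crossovers out of design keeps 20 evaluation cases and the 0.247 width. Leaving them out of evaluation instead gives 0.681–0.998 (width 0.318) for 14/15, 0.692–1.000 (0.308) for 10/10, and 0.478–1.000 (0.522) for 5/5.

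**The case against.** - **Entry is only offered.** Uptake is not stated, and no sentence says that crossovers' data will be used in design. A reader might infer that the cohorts will share patients and that accuracy will be inflated. The article supports only that this can happen and that nothing stated prevents it.
- **A condensed article may omit a separation rule.** The full protocol may contain one. That is fair, but the article itself describes the route from evaluation cohort to design cohort and back, so the point does not rest on silence alone.
- **The purpose of DOORS-M.** Study design describes its signatures as serving a recurrence test, and the step from DOORS-M design to DOORS-D accuracy appears in the Abstract. The Abstract is nevertheless explicit on it.
- **The samples differ.** DOORS-M blood from a crossover is drawn after diagnosis, DOORS-D blood before surgery. This weakens the link. Patient and tumour are the same, so independence is not restored.
- **The ceiling is not a likely effect.** The Introduction says that the proportion of cases with detectable ctDNA is unknown. A woman with none in her pre-operative plasma can be missed whatever shaped the test. It would be wrong to read 0.70 becoming 1.00 as an expected result.
- **The estimate is developmental.** In Table 1 the ctDNA test is a secondary objective of DOORS-D, accuracy is reported descriptively, and the Discussion foresees a trial in a larger population. This reduces the consequence. It does not remove overlap from the DOORS-D estimate.

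**Conclusion.** The concern holds conditionally. As written, the plan lets DOORS-D sarcoma cases help to design the test whose sensitivity they then measure. To the extent that they enter DOORS-M and their data are used, DOORS-D sensitivity would be optimistically biased. Overlap can reach all 20 planned sarcomas. The size of the bias depends on uptake, on the share of cases with detectable ctDNA and on a technique not yet chosen, so it cannot be computed; the figures in the table are ceilings under assumed values.

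Two wider readings are not supported. One is that accuracy in general is inflated: only sarcoma and STUMP patients cross over, so specificity for fibroids is untouched by this route, and overall accuracy is affected only through sensitivity. The other is that only 7–10 cases are at issue: that is a yearly count, giving about 18–26 over recruitment, and would be a total only if DOORS-D enrolled about 50 consecutive referrals at the centre's usual ratio.

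**What to change.** State in the protocol that:

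1. tumour whole exome sequencing and all plasma data from DOORS-D participants who enter DOORS-M are excluded from the data used to design the diagnostic test;
2. the test, including its positivity threshold, is locked on the remaining DOORS-M participants before it is applied to any DOORS-D plasma;
3. crossovers still count for DOORS-M's descriptive profiles and its recurrence objective.

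If the full protocol already has such a rule, citing it is enough. The rule must be fixed before design of the test begins.

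The text costs a sentence or two. The design set loses up to about 20 cases, and reported sensitivity may be lower. Because DOORS-M recruits no fibroid patients, the threshold would also have to be set without fibroid plasma from DOORS-D. The 20 evaluation cases and the planned precision are kept, whereas removing crossovers from the evaluation afterwards would widen the interval as shown above.
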